## Abstract

**Background:**

Cardiovascular disease (CVD) is a leading cause of hospitalization and death around the world. The prevalence of CVD is increasing and, therefore, development and investigation of effective programs to help people better self-manage their CVD and prevent secondary complications are needed.

**Objective:**

In this paper, we report on a protocol to evaluate Healing Circles—an evidence-based and patient-informed peer support mobile health program designed to facilitate self-management and support patients in their recovery from and management of CVD. We hypothesize that individuals with CVD who use Healing Circles will experience greater improvements to their self-management ability than individuals receiving usual care.

**Methods:**

In this single-blinded (assessor) randomized controlled trial, 250 community-living individuals with CVD will be randomized on a 1:1 basis to either Healing Circles or Usual Care. The primary outcome of self-management will be measured using the Health Education Impact Questionnaire version 3.0. Secondary outcomes include self-efficacy with chronic disease management, health-related quality of life, health resource use and costs, and electronic health literacy. Measurements will be taken at the baseline and every 6 months for 24 months.

**Results:**

The study started recruitment in September 2017. Individuals are currently being recruited for participation, and existing participants are currently on follow-up. Measurements will be taken every 6 months until the study end, which is anticipated in December 2019.

**Conclusions:**

Healing Circles is a novel program aimed toward improving self-management through peer support. Given our real-world study design, our findings will be readily translatable into practice. If the results support our hypothesis, it will indicate that Healing Circles is an effective intervention for improving self-management and reducing health care use.

**Trial Registration:**

ClinicalTrials.gov NCT03159325; https://clinicaltrials.gov/ct2/show/NCT03159325 (Archived by WebCite at http://www.webcitation.org/74DvxVKUd)

**International Registered Report Identifier (IRRID):**

DERR1-10.2196/12322

## Introduction

Cardiovascular disease (CVD) is a leading cause of hospitalization and death around the world [1]. In 2015, 17.7 million people died from a CVD (7.4 million due to coronary artery disease), representing 31% of all deaths worldwide [1]. In the United States, >90 million people are reported to have a CVD, with total direct costs of medical care exceeding US$396 billion in 2012 [2]. Owing to population aging and the rising epidemics of obesity and type 2 diabetes, it is anticipated that the CVD number will continue to grow, along with annual costs that are estimated to reach US$918 billion by 2030 [2].

Patient self-management, defined as an individual’s ability to manage the symptoms, treatment, physical and psychosocial consequences, and lifestyle changes inherent in living with one or more chronic conditions [3], is a cornerstone of treatment for CVD [4]. At present, it is estimated that half of the CVD-related hospital readmissions are due to patients not effectively self-managing their CVD [5,6]. Enhancing patient self-management, therefore, can help prevent patient deterioration and downstream hospitalizations for CVD, as well as reduce health care costs and premature mortality [7-9]. Importantly, patients who adopt self-management practices are empowered with the skills and knowledge necessary to manage their condition for long-term health benefits [7,10]. A key element of effective self-management support includes access to social and peer support networks [10-12]. Patients with CVD who report poor social support have higher readmission rates [13-15] and increased risk of mortality [16-18]. Social support programs that facilitate patients sharing information can reduce depression, provide comfort, restore confidence, improve functional status, and offer practical solutions for self-management [19], which, in turn, can result in lower rates of premature mortality [20] and fewer subsequent CVD events [21].

Despite benefits from self-management programs, questions remain as to how these programs can be implemented. Much discussion has centered on integrating self-management within the health care systems in Canada and the United States [12,22,23]. However, the integration of support for self-management practices into these health care systems has been slow, primarily due to the inherent challenges of systems that have traditionally emphasized the management of acute and episodic conditions rather than the chronic and continuous care patients with CVD require [12,22]. Without the development and testing of accessible and effective self-management programs to help people better manage their CVD and prevent secondary complications, the burden of the disease is likely to reach insurmountable levels.

In this study, we report the protocol of a real-world randomized controlled trial to evaluate Healing Circles—a mobile health (mHealth) self-management and social support program designed to bring peers with CVD together to learn from and support each other in the recovery and daily management of their disease. The primary hypothesis of this study is that individuals with CVD who participate in Healing Circles will experience improvements in their self-management ability, which are significantly greater than individuals receiving usual care. We are also investigating the effects of Healing Circles on the health-related quality of life, self-efficacy with chronic disease management, electronic health (eHealth) literacy, and health care resource use as part of our economic evaluation.

## Methods

### Study Design

This multisite study uses a randomized, controlled, parallel-group, single-blinded (assessor) study design, which has been guided by our Healthcare Innovation Community advisory group of researchers, clinicians, patients, and decision makers. This study has been registered on ClinicalTrials.gov (#NCT03159325). The reporting of this protocol follows the Standard Protocol Items: Recommendations for Intervention Trials [24] guidelines. Figure 1 presents an overview of trial procedures.

### Patient Population

Volunteers from British Columbia, Canada, will be recruited from cardiac outpatient clinics and community-based CVD support groups. Individuals will be included for study if they (1) have a CVD (ischemic heart disease, atrial fibrillation, heart failure, or patients with implantable cardioverter-defibrillator; together these are nearly 80% of patients with CVD); (2) are aged ≥19 years; (3) own or have regular access to either a smartphone (Android or iOS operating system), tablet, or laptop or desktop computer; and (4) can speak, write, and comprehend English. Individuals will be excluded if they (1) have cognitive or physical impairments that may interfere with effective interaction with the Healing Circles program; (2) have a known planned surgical intervention; (3) have another household member in the study; or (4) are unable to provide informed consent.

### Sample Size Estimate

Data from our single-group, pre-post pilot study that examined the proof-of-concept of the Healing Circles program [25] indicated an expected effect size of 0.58 in our primary outcome, the difference in the change in the social integration and support subscale of the Health Education Impact Questionnaire (HeiQ) Version 3 [26]. For this study, we selected a more conservative effect size of 0.33 that is, a mid-to-large effect based on Cohen *f* mid effect (0.25) plus large effect (0.40) divided by 2 [27] to account for comparison between the 2 groups (of note, this estimate may increase slightly in the Usual Care group) and the fact that the parameter estimates from our small pilot study may be highly variable. With an alpha of.05, we calculated a sample size of 198 to have 90% power. To adjust for an expected loss to follow-up rate of ~20%, over the duration of the study, we will recruit a sample size of 250 (125 per group) to retain 198 participants at the study end.

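### The planning effect size of 0.33, the 198 participants and the 90% power do not fit together, and the scales of 0.33 and of the pilot 0.58 are not reconciled

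*Protocol article*

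**What the plan says.** All the relevant text is in the protocol article, Methods, Sample Size Estimate, unless noted.

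- The single-group, pre-post pilot "indicated an expected effect size of 0.58 in our primary outcome". The section does not say whether this is a d, a paired d or an f.
- For the trial, "we selected a more conservative effect size of 0.33 that is, a mid-to-large effect based on Cohen" f. The derivation is given as "mid effect (0.25) plus large effect (0.40) divided by 2".
- The reasons given for a smaller value are that the trial compares two groups, that Usual Care may improve slightly, and that estimates from a small pilot are unstable.
- "With an alpha of.05, we calculated a sample size of 198 to have 90% power". The test, the sidedness, and any standard deviation or correlation are not given.
- After an allowance for about 20% loss, "we will recruit a sample size of 250 (125 per group) to retain 198 participants at the study end".
- The Abstract (Methods) says participants "will be randomized on a 1:1 basis to either Healing Circles or Usual Care". Under Statistical Analyses, the primary comparison is the between-group difference in change, from a mixed-effects model with repeated measures.

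**The concern.** The section prints an effect size, its derivation, alpha, power and N, so a reader can check whether they agree. Two things do not.

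First, 0.33 is expressly an average of Cohen f benchmarks. With two groups, f is half of d, so the same number means a very different effect depending on the scale. The N of 198 fits neither scale at 90% power.

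Second, 0.33 is ranked below 0.58 without showing that the two are on the same scale.

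This paragraph is the article's only justification for 250 participants. A reader who takes 0.33 as an ordinary standardised difference, as its placement beside 0.58 invites, will believe that the trial has 90% power for a third of a standard deviation. If a null result follows, it will be read with that confidence.

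**Working it through.** **Inputs.** From Sample Size Estimate: alpha 0.05, power 90%, effect size 0.33 (mean of f = 0.25 and 0.40), 198 analysed, 250 recruited, loss about 20%. From the Abstract: 1:1 allocation, so 198 is 99 per arm. Assumption: two-sided test. One-sided results are also given.

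**Step 1: the scale.** (0.25 + 0.40)/2 = 0.325, rounded to 0.33. Cohen f is the standard deviation of the group means divided by the within-group standard deviation. Two equal groups that differ by d lie at ±d/2 around their mean, so f = d/2. Hence f = 0.33 means d = 0.66 (0.65 without rounding).

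**Step 2: try to reproduce 198.** Normal approximation, per arm: n = 2(1.960 + 1.282)²/d² = 21.01/d². The exact totals use the noncentral t with equal arms.

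| Reading of 0.33 | n per arm (normal) | Total (normal) | Total (exact t) | One-sided total |
|---|---|---|---|---|
| f, so d = 0.66 | 21.01/0.4356 = 48.2, so 49 | 98 | 100 | 80 to 82 |
| d = 0.33 | 21.01/0.1089 = 192.9, so 193 | 386 | 388 | 316 |

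The two-group F test with f = 0.33 gives 99 in total if the arms need not be equal. Unrounded, f = 0.325 needs 102 and d = 0.325 needs 400. None of these is 198.

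**Step 3: power at 99 per arm.** Noncentrality = d√(n/2) = d × √49.5 = 7.036d.

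- d = 0.66: 4.64 − 1.96 = 2.68, so power is 99.6%.
- d = 0.33: 2.32 − 1.96 = 0.36, so power is 64% (exact 63.7%; one-sided 75%).
- d = 0.33 with all 250 analysed: 0.33 × √62.5 = 2.61, so power is 74%.
- Effect detectable with 90% power: exact d = 0.463, which is f of about 0.23. With 80% power: d = 0.400.

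**Step 4: where 198 could come from.** The number 99 arises in two ways: as the total for f = 0.33, and as the one-sample (paired) sample size for a standardised change of 0.33. Doubling either gives 198. Doubling the first counts a total as if it were per arm. The second tests change within a group, not the difference between groups. Also, 198 lies close to the per-arm need for d = 0.325 to 0.33 (194 to 200 exact). The text does not show which route, if any, was taken.

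**Step 5: the loss allowance.** 198/0.80 = 247.5, so 248, and 250 is consistent with it. The problem lies before this step.

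**Step 6: the comparison with 0.58.** If 0.58 is d-type, then 0.66 > 0.58. Treated as between-group effects, d = 0.58 needs 128 in total and d = 0.66 needs 100, so the planning value would ask for fewer participants than the pilot value. If 0.58 is an f, it equals d = 1.16 and 0.33 is indeed smaller.

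**The case against.** The strongest reply is that f is the only scale the section names. On that scale 198 gives 99.6% power, so the trial has more than it claims. This stands. A reader might infer that 198 falls short of 90% on either reading; that is wrong. The shortfall arises only if 0.33 is a d, which the article does not say. What remains is that 198 is not the number that corresponds to 90% on either reading.

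A second reply is that the metric of 0.58 is unknown, and that a single-group pre-post effect and a between-group d have different denominators. This also stands. A reader might infer flatly that 0.33 is less cautious than the pilot value, but the article supports that only conditionally. A d-type value is plausible for a single-group pilot, and if so the ranking is reversed. The missing metric is itself part of the problem, because the article ranks two numbers without a shared scale.

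A third reply is that 64% ignores the planned mixed-effects model. Suppose 0.33 is a d on the raw-score standard deviation, and the analysis adjusts for baseline and averages m follow-ups with a common correlation r. The required total is then 388 × [(1 + (m − 1)r)/m − r²]. This gives:

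- m = 1, r = 0.5: 388 × 0.75 = 291
- m = 1, r = 0.7: 388 × 0.51 = 198
- m = 2, r = 0.5: 388 × 0.50 = 194
- m = 4, r = 0.7: 388 × 0.285 = 111

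So some assumptions do lead to about 198. The article states none of them, and it presents 0.33 as an f. The reply shows that 64% is not the power of the planned analysis. It does not show how 198 was obtained.

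**Conclusion.** The concern holds: effect size, N and power as printed do not agree. At two-sided 0.05 and 90% power, 198 is about twice what f = 0.33 requires (99 to 100) and about half of what d = 0.33 requires (388). In an unadjusted two-group comparison, 198 matches 90% power only at d of about 0.46, which the article does not give. A one-sided test does not reconcile the figures.

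A reader might conclude that the trial is underpowered. The article does not support that as a plain statement. Power at 198 is 99.6% on the scale it names. It is 64% only if 0.33 is a d and the comparison is unadjusted at one timepoint. In that case the chance of missing a true effect of 0.33 is about 36%, not the 10% implied. The claim that 0.33 is the more cautious value is unsupported as written, and it is wrong if the pilot 0.58 is d-type.

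This is an error in figures that the article prints, not detail left to a fuller document.

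**What to change.** Keep 250 and rewrite the paragraph:

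1. Name the metric of the pilot 0.58 and express it and the planning value on one scale. Otherwise, delete both the claim of greater caution and the averaging of Cohen f benchmarks.
2. State the test, the sidedness and any within-person correlation assumed for the mixed-effects model. If 198 came from a repeated-measures calculation, give its inputs.
3. Restate the power. Possible wording, if no such calculation exists:

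> With 99 per arm analysed and two-sided alpha 0.05, an unadjusted two-group comparison of change has 90% power for a standardised difference of 0.46, 80% for 0.40 and 64% for 0.33. The mixed-effects model may do better, depending on the within-person correlation.

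The cost is one paragraph. Recruitment, arms and analysis stay as they are, and no participants are added. The drawback is that the stated power may look less favourable than the present 90%.

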**Figure 1 figure1:**
[figure not shown]
Overview of trial procedures.

### Randomization and Interventions

After the baseline assessment, participants will be stratified by sex and recruitment site, and randomized using Web-based, computer-generated, random block sizes of 4 and 6 in a 1:1 manner to either the Usual Care or the Healing Circles group. A member of the research team who is not involved with recruitment, assessments, or study intervention will perform the randomization procedures.

#### Usual Care Group

Participants randomized to the usual care group will receive a list of internet-based resources appropriate for their specific CVD. For many participants, usual care will comprise the care provided by their family physician. By virtue of our recruitment, some participants will be attending cardiac outpatient clinics and may receive some self-management education as a result. However, participants are unlikely to have access to formalized peer support programs or regular access to expert input or advice. There will be no contact between the study personnel and Usual Care participants for the study duration or any attempt to influence any aspect of patient care.

#### Experimental (Healing Circles) Group

In addition to receiving care as usual, participants randomized to the intervention group will receive access to and instruction on how to use (ie, provision of an on-boarding document) the Healing Circles program. Healing Circles is a novel, evidence-based, and patient-informed self-management platform designed to support patients with CVD. It uses a private, secure social network that helps connect participants and provides functions to assist participants in self-management through evidence-based principles of behavioral change (eg, social support [11] and self-monitoring [28]).

Healing Circles has 3 following layers: (1) the participant; (2) the participant’s circle, and (3) the broader Healing Circles community. The participant’s circle is the private group that consists of other Healing Circle users that a participant chooses to support him or her (ie, an online support group). These private circles are used for private group or one-on-one chat and communication, peer support, challenges, and sharing. The broader community comprises all Healing Circles users, where participants can see public posts from others not in their circle.

Participants access Healing Circles by downloading or installing, at no cost, the platform onto their personal device (smartphone or tablet). Upon initiating Healing Circles, participants are asked to enter optional information about themselves such as gender, age, cardiac condition, region of residence, types of treatments, and personal interests and hobbies. This information allows the platform to customize and personalize the user experience, from suggesting peers with whom to connect with and add to their support circle, to personalizing content and customizing management tracking tools. However, entering this information is optional and is kept private and secure in accordance with Canadian and American data privacy laws (ie, Personal Information Protection and Electronic Documents Act in Canada and the Health Insurance Portability and Accountability Act in the United States). The participants’ next step is to form their own circle of 8-10 “friends”. Social support is strongest when coming from peers who have similar characteristics and who possess knowledge that is pragmatic and derived from similar lived experiences [19], so Healing Circles offers participants a matching algorithm that can be used to identify similar users to invite to their Circle. The proprietary algorithm is capable of matching from one to several users that help participants develop their Circle. In addition, participants can be invited into other Circles by other users (participants can be in more than one Circle). Similarly, this matching algorithm also matches participants to relevant evidence-based content on Healing Circles, thereby providing a personalized experience. While we will advise participants to use Healing Circles at their own convenience, we will encourage them to create their Circles within 1 week to minimize the time from the baseline assessment and first use. Participants will be instructed to contact the program developers if they experience issues using the program.

Participants also have access to evidence-based educational materials on CVD as well as several functions such as *self-initiated reminders*, which participants can sign themselves up for. These simple reminders are push notifications to prompt participants to enter data. For example, participants can sign up for daily reminders to take their medication and, when prompted, can indicate if they have taken their medication. Furthermore, Healing Circles allows participants to track their progress and adherence to things like lifestyle behaviors and medication (*health tracking*) and to pose *daily challenges* to individuals in their Circle, their entire Circle, or the entire community; these challenges can serve to motivate participants to be active in their health and social network.

### Study Outcome Measures

The primary outcome is the difference in the change in the social integration and support subscale of the HeiQ Version 3 [26] between the Healing Circles and Usual Care groups. HeiQ is a self-management measure developed using Item Response Theory, comprising 8 self-management subscales as follows: health directed activity (4 items); positive and active engagement in life (5 items); emotional distress (6 items); self-monitoring and insight (6 items); constructive attitudes and approaches (5 items); skill and technique acquisition (4 items); social integration and support (5 items); and health service navigation (5 items). Each item is scored using a 4-point response scale (1=strongly disagree; 2=disagree; 3=agree; 4=strongly agree). A mean score is derived for each subscale with higher scores indicating better self-management ability, with the exception of the emotional well-being subscale where a higher mean score is indicative of lower self-management ability.

We selected the 5-item social integration and support subscale as our primary outcome because the items align closely with the Healing Circles intervention, and results from our pilot study suggested that this subscale is most responsive to changes as a result of the Healing Circles program [25]. Moreover, this subscale has been shown to have high internal consistency reliability (Cronbach alpha=.86) [26].

Secondary outcomes include the 7 other subscales within the HeiQ as well as several other variables as follows. *Self-efficacy* will be measured using the 6-item Self-efficacy for Managing Chronic Disease Scale [29]. This 6-item scale covers several domains that are common across many chronic diseases, including symptom control, role functioning, emotional functioning, and communicating with physicians and has high internal consistency reliability (Cronbach alpha=.91) [29]. Responses for each item range from 1 (not at all confident) to 10 (totally confident). Higher mean scores indicate higher self-efficacy.

Generic preference-based measures of *health-related quality of life* and *capability well-being* will be collected using the EuroQoL-5 dimension 5-level version (EQ-5D-5L) [30] and ICEpop CAPability measure for Adults (ICECAP-A) [31], respectively. These two measures will be used in the economic analysis (see below). The EQ-5D-5L is a widely used outcome measure for the estimation of quality-adjusted life years (QALYs). Developed by the EuroQol Group, the EQ-5D-5L was introduced to improve the sensitivity as compared with the EQ-5D 3-level version [32]. The ICECAP-A is based on Amartya Sen’s capability approach, which distinguishes between capabilities and achieved functioning [31]. It accounts for the fact that a person’s capabilities (what a person can do) may differ from their functioning (what a person actually does), and goes beyond health-related aspects of the quality of life. Both EQ-5D-5L and ICECAP-A have been validated in a range of clinical contexts [33-36].

*Health care resource use* data will be collected from a combination of medical records and self-report questionnaires. The self-report questionnaires will be variants of versions that have been used in previous trial-based economic evaluations [37-39]. Data collection will focus on key cost drivers, such as hospital attendances (inpatient stays, outpatient appointments, and any other hospital visits to health care practitioners), consultations with primary health care providers (eg, family doctors and nurse practitioners), and prescribed medications. Details of nonhealth care costs will be collected, including out-of-pocket expenses, periods of work absence, as well as an assessment of the use of other mHealth -based applications. The dollar value of all resources will be estimated from a number of sources, including local health authority accounts data, Canadian Institute for Health Information patient cost estimator for acute sector admissions [40], and self-reported costs.

*Usage of Healing Circles* will be assessed by tracking the frequency of using Healing Circles features (eg, log-ins and the frequency of use of various platform features) using program metrics. Furthermore, we will assess what devices participants used to access the platform, as well as engagement and communication with other Healing Circles users.

Finally, *participants’ perceptions, attitudes, and satisfaction* with Healing Circles will be assessed using qualitative interview methodologies at the end of the study. A subgroup of 20-30 participants in the Healing Circles group will be recruited and taken through semistructured, open-ended interviews to explore their experiences and the factors that influence acceptance and the use of the Healing Circles program. Potential interview participants will be identified by stratified purposeful sampling, with representation from both sexes, type of CVD, urban or rural residence, and highly active and less-active Circles. A 3-stage analysis of interview transcripts (open-coding, axial coding, and selective coding) will be guided by an inductive iterative approach [41,42]. The interviews will be conducted by phone and recorded and transcribed with personal identifiers removed.

